### Secondary outcome measures

#### Change in intention to initiate tobacco use

To assess the change in intention to initiate tobacco use, a two-item 4-point Likert scale will be used: (1) “if someone (cousin/friend/close relative) offers you a tobacco product, would you use it?” and (2) “at any time during the next 12 months, do you think you will use any form of tobacco?” Responses will range from “Definitely not,” to “Definitely yes”, with scores ranging from 0 to 6. Lower scores indicate a lower likelihood of intending to initiate tobacco. The potential effect of the intervention will be determined by changes in scores between baseline and follow-up.

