#### Secondary objectives

To evaluate the potential efficacy of IATIP in preventing tobacco initiation as indexed by intention to use among school adolescents.To examine the effect of IATIP on promoting health and well-being in the adolescents.To explore changes in tobacco-related knowledge, attitudes, beliefs, and skills to resist tobacco.To conduct a process evaluation to understand the implementation, facilitation, and participant experiences of the IATIP.

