### Study participants and eligibility

The trial will recruit students enrolled in years 8 and 9 in schools across Dhaka. Eligible participants must meet the following criteria: (i) be Bangladeshi school-going adolescents; (ii) be enrolled at one of the participating schools; and (iii) be in year 8 or 9. Exclusion criteria include (i) students unwilling to participate; (ii) students unable to provide informed consent (including parental consent); and (iii) students with severe cognitive or physical impairments that hinder participation or completion of assessments (as determined in consultation with school teachers).

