		2.3	Discover positive and healthy alternatives to using tobacco	Group discussion word cloud game (group activity)	Students will explore and identify positive and healthy alternatives to tobacco use	Discussion Collaboration Production
3	Mind Matters: Navigating Emotions and Setting Goals for a Tobacco-Free Future	3.1	Links between tobacco and mental wellbeing	–	Students will gain an understanding of what mental well-being is, its significance, and how it relates to tobacco use prevention	Acquisition
		3.2	Coping with emotions: expression of negative feelings, dealing with stress, depression and anxiety	Deep breathing exercise	Students will develop skills to build emotional resilience, cope with stress, depression and anxiety, and manage emotions without turning to tobacco use	Acquisition Practice
		3.3	Goal setting and personal commitment (pledge) not to use tobacco	Open discussion Written pledges, and artwork (poster contest)	Students will be able to set clear and achievable goals related to tobacco use behaviour, whether it is becoming a tobacco non-user or achieving tobacco cessation. And also, students will reinforce their commitment to a tobacco-free lifestyle and how it will contribute to their well-being	Discussion Investigation Production

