### Procedure

#### Recruitment

A pool of 24 secondary and higher secondary schools in Dhaka, representing the most common type of school following the National Curriculum and Textbook Board (NCTB) curriculum in Bangla, was invited to participate. This sampling strategy enhances generalizability across the Bangladeshi school system. Half of the invited schools agreed to participate, from which eight schools will be randomly selected. All eligible year 8 and year 9 students within these schools will be included in the study. Invitation letters will be sent to school authorities, and information sheets and consent forms will be distributed to students and their parents or guardians. The final list of participating schools, classes, and students will be confirmed based on eligibility criteria.

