#### Tobacco use behaviours

The standard of Global Youth Tobacco Survey (GYTS) will be applied for the calculation of tobacco use prevalence [51]. The estimates of tobacco use will derive from six questions, resulting in three measures: current user, ever user, and non-user. A tobacco user will be defined as someone who is currently using ≥ 1 tobacco product (combustible: cigarettes, pipes, cigars, waterpipes, hookah, shisha, bidis, and non-combustible: tobacco leaf, gul, zorda with pan, khaini, and pan-masala). Current tobacco user includes daily and occasional tobacco user in the past 30 days preceding the data collection. Ever tobacco user will be defined as someone who has consumed ≥ 1 tobacco product during their lifetime. Non-user will be defined as someone who has never used any tobacco products.

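### The intention-to-initiate outcome is scored from items about use and is not restricted to baseline never-users, so its all-pupil effect cannot by itself show prevention of initiation

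*Protocol article*

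**What the plan says.** The secondary objective in the Protocol article is "To evaluate the potential efficacy of IATIP in preventing tobacco initiation as indexed by intention to use among school adolescents". The outcome section is headed as change in intention to initiate, and interprets the score accordingly: "Lower scores indicate a lower likelihood of intending to initiate tobacco". The score comes from two four-point items. One asks whether the pupil would use a tobacco product offered by someone close. The other asks "at any time during the next 12 months, do you think you will use any form of tobacco". Neither refers to first use.

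Study participants and eligibility requires only that pupils "i) be Bangladeshi school-going adolescents; (ii) be enrolled at one of the participating schools; and (iii) be in year 8 or 9". The exclusions concern willingness, consent and impairment, not tobacco use. Recruitment adds: "All eligible year 8 and year 9 students within these schools will be included in the study". Table 1 (session 3.3) expects some users, since its goal-setting outcome covers pupils "whether it is becoming a tobacco non-user or achieving tobacco cessation".

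The Analysis section specifies a mixed-effects model for intention to use tobacco, with baseline covariates, under intention-to-treat. It does not restrict the model by tobacco history. The named subgroups include tobacco use by family or friends but not the pupil's own use; the list is open-ended.

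The group that could initiate is already defined, under Covariates: "Non-user will be defined as someone who has never used any tobacco products".

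**The concern.** Only a pupil who has never used tobacco can initiate. A current user who answers yes to both items is reporting an intention to carry on, and a former user an intention to resume. The interpretation that the protocol gives to the score is therefore wrong for these pupils, yet they enter the model that serves the prevention objective.

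Two things are at stake. First, a fall in the all-pupil score could come from users intending to stop, from never-users becoming more resistant, or from both, and a single estimate does not separate them. The curriculum addresses both groups, so this is a practical possibility. Second, Sample size calculations says the pilot should inform the variability of outcomes for a full trial. An SD or ICC from a mixed population is not that of a never-user prevention population. User share may also differ between schools: the protocol's use figures are 13.8% for boys and 2.0% for girls, and schools are blocked as girls-only, boys-only or mixed.

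**Working it through.** **The plan's own figures.** The article gives no calculation for the intention outcome; that is in Additional file 2, which is not shown. The one sample-size figure that can be reproduced is the retention precision: 1.96 × √(0.85 × 0.15 / 1280) = 0.0196, or 1.96 percentage points, matching the stated ±2.0%. This is a simple binomial half-width that ignores clustering. It says nothing about the intention score.

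**Number of users.** Inputs: N about 1280 (Sample size calculations); use 9.8% overall, 13.8% in boys and 2.0% in girls (Background, from a 2014 national school survey).

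| Share of users | Users among 1280 | Pupils left |
|---|---|---|
| 2.0% | 0.020 × 1280 ≈ 26 | 1254 |
| 9.8% | 0.098 × 1280 ≈ 125 | 1155 |
| 13.8% | 0.138 × 1280 ≈ 177 | 1103 |

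These counts take the survey figures as current use. Ever users include current users, so the number who cannot initiate is at least as large at any given current-use rate. The protocol gives no ever-use rate. If it were 15% to 25% (assumption), 192 to 320 pupils could not initiate and 1088 to 960 would remain.

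**What the all-pupil effect estimates.** With p the share of users, equal in both arms, the all-pupil effect is D = (1 − p) × d_never + p × d_user. The effects below are assumed, in points on the 0–6 score.

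| p | d_never | d_user | D | Part from users |
|---|---|---|---|---|
| 9.8% | 0 | −2 | 0.098 × (−2) = −0.20 | all |
| 9.8% | −0.2 | 0 | 0.902 × (−0.2) = −0.18 | none |
| 9.8% | −0.2 | −1.0 | −0.180 − 0.098 = −0.28 | 35% |
| 13.8% | −0.2 | −1.0 | −0.172 − 0.138 = −0.31 | 44% |

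The first two rows are opposite answers about prevention, yet the all-pupil estimates differ by less than 0.02 points.

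**Effect on the SD.** Assume never-users have mean 0.3 and SD 0.8, users have mean 4.0 and SD 1.0, and p = 9.8%.
- Within-group variance: 0.902 × 0.64 + 0.098 × 1.0 = 0.675, so the pooled within-group SD is 0.82, or 3% above 0.8.
- Between-group variance: 0.902 × 0.098 × 3.7² = 1.21.
- Total variance: 0.675 + 1.21 = 1.89, so the raw single-time SD is 1.37, or 72% above 0.8.
- With a user mean of 2.5: 0.675 + 0.0884 × 2.2² = 1.10, SD 1.05, or 31% above 0.8.

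Nearly all the inflation comes from the gap between group means. Adjusting for use status removes that gap, and a stable gap cancels in change scores.

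**The case against.** The strongest reply is that the all-pupil estimate is a legitimate target. The objective is worded as intention to use among school adolescents, the model is for intention to use, and the programme goes to whole year groups without selection on use. That stands as a defence of keeping the all-pupil analysis. It does not rescue the reading of the score as intention to initiate, or its use alone as evidence of prevention.

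The analysis population is also inferred. No sentence says that users are included in this outcome; it follows from eligibility, recruitment and unrestricted intention-to-treat. An analysis plan or Additional file 2 might restrict it, which cannot be checked. But the article itself fixes the objective, items and interpretation, and these do not agree.

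Tobacco use is listed among the covariates. Adjusting for it reduces residual variance but still gives one effect averaged over users and never-users. The open subgroup list means a reader should not infer that analysis by own use is ruled out; equally, it does not pre-specify one.

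A reader might infer that the planning SD will be inflated by some 70%. The documents do not support that. The score means are assumed, the figure applies to an unadjusted score at one time point, and the planned analysis concerns change and adjusts for baseline covariates.

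The user count is soft. The survey is national and dates from 2014, and 9.8% implies about 66% boys: (9.8 − 2.0) / (13.8 − 2.0). An even sex split would give 7.9%, or about 101 users. The trial's sex mix is not stated.

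**Conclusion.** The point holds as a mismatch between objective, outcome label and analysed population. Followed as written, the analysis blends prevention among never-users with intention to continue or resume among users. That users would be admitted rests on the protocol's own text; their number, about 125 of 1280 with a range of 26 to 177, rests on applying its survey figures to this sample. The similarity of −0.20 and −0.18 rests on assumed effects and shows only that the two cases cannot be told apart. The raw SD and ICC would not be those of a never-user population, though adjustment for baseline use or score would remove much of the SD inflation.

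The importance is moderate. The outcome is secondary and exploratory, the primary outcome is feasibility, and no progression criterion uses the intention score. A reader might infer that the efficacy analysis is invalid or that the decision to progress is compromised; neither follows. What is affected is what the pilot can say about prevention, and the planning values it passes on.

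**What to change.** Pre-specify the initiation analysis in baseline never-users, using the existing non-user category from the baseline questionnaire and the same mixed model with the same small-sample correction. Because the restriction uses a baseline variable, it keeps the randomised comparison. Report the arm difference, SD and ICC in that group for planning the definitive trial. Keep the all-pupil analysis alongside it, labelled as intention to use tobacco, and report baseline current and ever users descriptively. If the never-user analysis is not wanted, at minimum rename the outcome and reword the objective so that neither claims initiation.

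The change is to wording and analysis only; recruitment and questionnaires stay as they are. The cost is a smaller analysis set: about 1155 pupils at 9.8%, fewer if ever use is common. The loss of precision cannot be quantified, because the article gives neither an ICC nor an ever-use rate. It should not be assumed negligible on the ground that between-school variation dominates, since nothing in the article shows that.

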#### Health and well-being

Health and wellbeing will be assessed using the following validated scales. To assess physical health state, students will rate their overall physical health on a 5-point scale, with higher scores indicating better health. Mental well-being will be measured using the Short Warwick–Edinburgh Mental Well-being Scale, with scores ranging from 7 to 35 [44, 45]. Perceived stress will be evaluated using the 10-item Perceived Stress Scale [46]. This widely recognised scale assesses the extent to which individuals perceive situations in their lives as stressful. Students’ anxiety will be assessed using the Generalized Anxiety Disorder-7 scale (GAD-7), a 7-item 4-point Likert scale, with scores ranging from 0 to 21 [30]. The Patient Health Questionnaire-9 scale (PHQ-9), a 9-item 4-point Likert scale, with scores ranging from 0 to 27, will be used to assess depression [47] These scales, chosen for their validity and reliability, offer a comprehensive evaluation of adolescents' mental health and well-being, encompassing positive aspects, perceived stress, anxiety, and depressive symptoms. The structured responses provided by students will contribute valuable data for understanding the effect of the IATIP on mental health outcomes.

#### Knowledge about tobacco and health

Students’ knowledge about tobacco and health will be assessed using 20 items adapted from a previous study [48]. A student will earn a point for each correct response, with a maximum score of 20.

#### Attitudes toward tobacco and health

Students’ attitudes toward tobacco and health will be measured using a 16-item standardized scale adapted from a previous study conducted in China [48]. Responses will be rated on a 5-point scale, with scores ranging from 16 to 80, and higher scores reflecting more negative attitudes toward tobacco. For positive attitude items, responses of “extremely agree” to “extremely disagree” will be scored as 5 to 1, whereas for negative attitude items, the scoring will be reversed to 1 to 5 points.

#### Beliefs about tobacco and health

Students’ beliefs about tobacco use will be assessed using an 8-item 4-point scale adapted from the EU-Dap questionnaire [49, 50]. This scale focuses on both positive (4 items) and negative (4 items) beliefs concerning various aspects of tobacco use. Positive beliefs include feeling relaxed, having fun, being popular, and being confident and outgoing. Negative beliefs encompass issues with parents and friends, financial problems, and the risk of addiction.

#### Skills for a tobacco-free healthy lifestyle

To comprehensively assess various skills contributing to a tobacco-free healthy lifestyle, multiple dimensions will be evaluated through distinct Likert-type scales. For ‘Decision-Making Skills’, students will respond to statements reflecting different approaches to decision-making, indicating their level of agreement (1 = strongly agree to 4 = strongly disagree) across five items. For ‘Refusal Skills’, students will navigate hypothetical situations, expressing their likelihood of refusal (1 = very likely to 4 = very unlikely) in response to three scenarios. ‘Self-esteem’ will be assessed through agreement with self-descriptive statements (1 = strongly agree to 4 = strongly disagree), encompassing ten items. ‘Poor Problem-Solving Skills’ will be assessed by responses to statements related to interpersonal dealings (1 = strongly agree to 4 = strongly disagree), consisting of five items. Lastly, ‘Assertiveness’ will be evaluated by considering the ease or difficulty students perceive in accomplishing certain tasks (1 = very easy to 4 = very difficult) across six scenarios. This multifaceted approach aims to capture insights into students’ skills, providing a holistic understanding of their capabilities related to maintaining a tobacco-free healthy lifestyle. The scales used for assessing ‘Decision-Making Skills’, ‘Refusal Skills’, ‘Self-Esteem’, ‘Poor Problem-Solving Skills’, and ‘Assertiveness’ were adapted from the EU-Dap questionnaire [49]. The EU-Dap questionnaire is a validated instrument in the field, providing a comprehensive framework for evaluating various skills relevant to tobacco prevention among adolescents.

### Covariates

#### Socio-demographic information

Socio-demographic information will be collected from all participating students through both open-ended and close-ended questions, including their age, sex, religion, weekly pocket money expenditure, place of living (e.g., hostel, rented house with parents, owned property with parents, and others), and family background (including paternal and maternal education levels). See the full questionnaire in the Additional file 1.

#### Tobacco use behaviours

The standard of Global Youth Tobacco Survey (GYTS) will be applied for the calculation of tobacco use prevalence [51]. The estimates of tobacco use will derive from six questions, resulting in three measures: current user, ever user, and non-user. A tobacco user will be defined as someone who is currently using ≥ 1 tobacco product (combustible: cigarettes, pipes, cigars, waterpipes, hookah, shisha, bidis, and non-combustible: tobacco leaf, gul, zorda with pan, khaini, and pan-masala). Current tobacco user includes daily and occasional tobacco user in the past 30 days preceding the data collection. Ever tobacco user will be defined as someone who has consumed ≥ 1 tobacco product during their lifetime. Non-user will be defined as someone who has never used any tobacco products.

#### Cost measures

All direct costs, including intervention delivery costs (based on materials purchased and researcher time), will be recorded. An estimation will then be calculated to determine whether the costs are realistic and feasible based on available funding and resources for the future large-scale definitive trial.

### Data management

To ensure data integrity, confidentiality, and security, strict measures will be implemented, complying with the Data Protection Act 2018 and General Data Protection Regulations. Participant-completed questionnaires will be securely stored after data entry in a locked cupboard in Bangladesh under SH’s control. An anonymous soft copy of the dataset will be stored in a password-protected computer at University College London for 10 years, facilitating future assessments.

### Progression criteria

To inform the decision on whether to proceed to a future definitive trial, pre-specified progression criteria will be applied using a traffic light system [52].

(i)Recruitment: achieving ≥ 80% of the planned school and student recruitment will be considered green (go), 60–79% amber (amend), and < 60% red (stop).(ii)Retention: follow-up completion rates of ≥ 85% will be considered green, 60–84% amber, and < 60% red.(iii)Intervention fidelity: delivery of ≥ 85% of the intended sessions with high adherence to protocol will be green, 60–84% amber, and < 60% red.(iv)Acceptability: if ≥ 80% of adolescents and teachers rate the intervention as acceptable or very acceptable, this will be green, 60–79% amber, and < 60% red.

These thresholds were informed by benchmarks reported in previous pilot or feasibility trials [53–55] and reflect the minimum requirements for a larger trial to be feasible, sufficiently powered, and methodologically robust. Findings will be interpreted in light of these criteria to decide whether the intervention is feasible for a larger definitive trial, whether modifications are required, or whether the trial should not progress.

### Sample size calculations

Formal sample size calculations are not typically required for pilot or feasibility studies [56]. The sample size for this trial was therefore guided primarily by feasibility considerations, particularly the need to estimate key parameters such as recruitment and retention rates, adherence to the intervention, and completeness of outcome data with acceptable precision. For example, with an overall sample of approximately 1280 participants (640 in each group), a retention rate of 85% could be estimated with a 95% confidence interval of ± 2.0%, providing a sufficiently precise estimate to inform planning for a future definitive trial [57, 58].

In addition to feasibility considerations, an exploratory calculation was conducted to provide a pragmatic estimate for recruitment targets and to assess the potential scale of a future definitive trial. This calculation, based on a potential efficacy outcome (intention to initiate tobacco use), is not intended to serve as the primary justification for the sample size. Instead, it offers supportive information by (i) demonstrating the plausibility of detecting an effect of interest, (ii) informing logistical planning and resource allocation, and (iii) providing preliminary data to estimate the variability of outcomes for a full-scale trial. For completeness, the details of this calculation are reported in Additional file 2.

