## Methods

### Trial design

This study employs a pilot cluster randomised controlled trial (C-RCT) design. The unit of randomization will be schools, with the ultimate aim of informing a full-scale C-RCT. In addition, a mixed-methods approach will be employed for the process evaluation.

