### Analysis

The primary focus of this pilot trial is feasibility. Descriptive analyses will be undertaken to profile baseline characteristics of both the intervention and control groups, and to assess key feasibility outcomes. These include rates of recruitment, consent, retention, and adherence, as well as indicators of intervention acceptability and engagement at both the cluster and individual levels. These feasibility outcomes will be reported with corresponding proportions, means, and 95% confidence intervals, where appropriate. Pre-specified progression criteria (see above) will be applied to determine the feasibility of proceeding to a definitive trial.

The unit of analysis will be the individual adolescent, although randomization occurs at the school level. Clustering by school and class will be accounted for in multilevel models. Exploratory analyses of potential intervention effects will also be conducted. For binary outcomes, binomial distributions will be used, while normal distributions will be applied for continuous variables. Assumptions of normality, homogeneity of variance, and linearity will be examined; if violated, appropriate transformations (e.g., logarithmic or square root) will be applied. For missing data exceeding 5%, patterns and mechanisms of missingness will be explored, with multiple imputation used as appropriate. Sensitivity analyses will be undertaken to examine the impact of missing data and outliers.

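### The ±2.0% precision quoted for 85% retention treats about 1280 pupils in eight schools as independent, so it is too favourable unless the school ICC for retention is almost zero

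*Protocol article*

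**What the plan says.** Under Sample size calculations, the protocol article says: "The sample size for this trial was therefore guided primarily by feasibility considerations". It lists recruitment, retention, adherence and data completeness as the quantities to be estimated. The only number offered in support is that, with about 1280 participants (640 per arm), "a retention rate of 85% could be estimated with a 95% confidence interval of" ±2.0%, which it calls precise enough to plan a definitive trial. A separate calculation on intention to use tobacco sits in Additional file 2, which is not shown; the article says that it "is not intended to serve as the primary justification for the sample size".

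Under Trial design: "The unit of randomization will be schools, with the ultimate aim of informing a full-scale C-RCT". Recruitment and Randomization give eight schools, four per arm.

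Under Analysis: "These feasibility outcomes will be reported with corresponding proportions, means, and 95% confidence intervals, where appropriate". Clustering by school and class is to be handled in multilevel models, and corrections for the small number of schools are specified for the efficacy models. Under Progression criteria, retention is green at 85% or more, amber at 60–84% and red below 60%.

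**The concern.** Pupils in the same school share a timetable and a follow-up session held in class time, so whether one is retained is likely to be related to whether classmates are. A half-width computed as if each pupil were an independent draw then understates the uncertainty. With eight equal schools, a 16-point fall in retention at a single school moves the overall rate by 16/8 = 2 points, which is the whole of the stated margin.

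Feasibility is the primary outcome, and this figure is the only number shown for the stated main basis of the sample size. The 85% in the example is also the green/amber boundary for retention, one of a set of thresholds said to "reflect the minimum requirements for a larger trial to be feasible, sufficiently powered, and methodologically robust". A reader planning the definitive trial would take a retention estimate near 85% as known to within two points, when the design may support a margin two or three times as wide.

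**Working it through.** **Inputs from the protocol article.** Retention p = 0.85 and N = 1280 (Sample size calculations); eight schools (Recruitment); mean school size m = 1280/8 = 160.

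**Assumed input.** The school ICC for retention. The document gives none, so 0.01 to 0.05 is used as a range. Through √(ICC × 0.85 × 0.15), this corresponds to a between-school standard deviation in true retention of about 3.6 to 8.0 points.

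**Step 1: reproduce the stated figure.** 1.96 × √(0.85 × 0.15 / 1280) = 1.96 × 0.00998 = 0.0196, or ±1.96 points, which rounds to ±2.0. The choice of binomial method makes no material difference: the Wilson and Clopper–Pearson intervals both run from 82.9% to 86.9%. One arm alone (n = 640) would give ±2.77, so the stated figure pools all 1280 pupils with a design effect of 1.

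**Step 2: how small must the ICC be?** Design effect DE = 1 + (m − 1) × ICC = 1 + 159 × ICC. A half-width that still rounds to 2.0 is at most 2.05 points, so with the normal multiplier the ICC must not exceed ((2.05/1.956)² − 1)/159 = 0.0006. That is a between-school standard deviation of √(0.0006 × 0.1275), about 0.9 points.

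**Step 3: allow for clustering.** Half-width = multiplier × √(0.1275/1280 × DE). The multiplier is 1.96 (normal) or 2.365 (t on 8 − 1 = 7 df). Effective N = 1280/DE. Ratios are to 1.96 points.

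| Assumed ICC | DE | Effective N | Half-width, normal (ratio) | Half-width, t on 7 df (ratio) |
|---|---|---|---|---|
| 0.001 | 1.16 | 1104 | ±2.11 (1.08) | ±2.54 (1.30) |
| 0.005 | 1.80 | 713 | ±2.62 (1.34) | ±3.16 (1.62) |
| 0.01 | 2.59 | 494 | ±3.15 (1.61) | ±3.80 (1.94) |
| 0.02 | 4.18 | 306 | ±4.00 (2.04) | ±4.83 (2.47) |
| 0.05 | 8.95 | 143 | ±5.85 (2.99) | ±7.06 (3.61) |

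Even with ICC = 0, an interval built from eight school-level proportions on 7 df has half-width 2.365 × 0.998 = 2.4 points.

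**Step 4: the interval at an observed 85%.** The stated figure implies about 83% to 87%. With t on 7 df it would be about 81% to 89% at ICC 0.01, and about 78% to 92% at ICC 0.05.

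Equal school sizes are assumed throughout; unequal sizes would widen the intervals further.

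**The case against.** **The size is assumed.** This stands. No ICC appears in the document, and at 0.001 the normal half-width is only 1.08 times the stated one. A reader might also join the extremes into a single factor of 1.6 to 3.6, but that mixes two multipliers. One method at a time gives 1.6 to 3.0 (normal) or 1.9 to 3.6 (t). That the interval is too narrow for any appreciable clustering does not depend on the range.

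**The analysis handles clustering.** In part. A reader might infer that the feasibility intervals will be computed without regard to schools. The document does not say so. The Analysis section reports feasibility at school and pupil level, refers to multilevel models, and gives no interval formula; that detail may sit in an analysis plan that is not shown. Whatever is planned for the analysis, nothing carries it back to the printed ±2.0%.

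**The progression decision is unaffected.** A reader might infer that a wider interval would turn green into amber. It would not. The criterion is worded on the observed completion rate, with no confidence-limit rule. An observed 85% lies on the boundary, so even a true ±2.0% would straddle it. At the widest half-width tabulated, the lower limit of about 78% is still far from the 60% stop threshold.

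**It is an example in a pilot that needs no formal calculation.** It is introduced as an example, but the article chose to justify its size by precision, and no other figure is given.

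**Only these eight schools matter.** The figure is offered for planning a later trial, and the Recruitment section claims generalisability across the school system. School-to-school variation therefore belongs in the interval.

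**Conclusion.** Wrong as written. The arithmetic is correct for 1280 independent pupils, but the design samples eight schools, and the stated precision is reached only if the school ICC for retention is almost zero. Under an assumed ICC of 0.01 to 0.05 and equal school sizes, the half-width is about ±3.2 to ±5.9 points (normal) or ±3.8 to ±7.1 points (t, 7 df). The t version is the more suitable with eight schools. The independence error follows from the document's own figures; the size of the understatement depends on the assumed ICC. The point concerns the printed precision and how securely a retention rate near 85% can be read. It does not show that a traffic-light classification would change, nor that the planned feasibility intervals are unadjusted.

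**What to change.** In Sample size calculations, replace the ±2.0% sentence with one that carries the design effect and labels the ICC as an assumption. For example: *Allowing for eight schools of about 160 pupils and an assumed ICC of 0.01 to 0.05, 85% retention is estimated to within about 4 to 7 percentage points (t, 7 df).* Then reword the claim that the estimate is precise enough for planning so that it matches this range.

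In Analysis, add a clause saying that confidence intervals for the feasibility outcomes make the same allowance for clustering by school. This makes explicit what the text leaves open.

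The cost is wording and a less favourable stated figure. No extra pupils or schools are needed, and the progression thresholds stay as they are.
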